### Control arm

Family physicians of the control arm participants will not be informed of their patients’ participation in the trial until the last visit at month 60. This helps to ensure that the care provided to the control group participants reflects as much as possible real-life primary care practice.

The control arm baseline measurements and blood samples are taken at partner hospitals and laboratories across Estonia, all blood analyses are done centrally at the Tartu University Hospital medical laboratory. Physicians are blinded to the results of baseline control arm measurements and analyses until the end of the trial. At month 60 of the trial, physicians will be informed about their patients who were in the control arm for scheduling a final study visit. During the final trial visit, the physicians will inform participants of their CAD PRS, provide counselling and take final measurements.

### Criteria for discontinuing or modifying allocated intervention

This trial involves investigative medicinal products (IMP) licensed in the European Union and are being used within their licensed range of indications, dosage and form. Therefore, no higher risk than the risk of standard medical care is associated with the IMPs and the EE-PRS trial does not include any formal safety endpoints nor the documentation of adverse events. Therefore, the investigators of this trial will collect and report adverse drug reactions (ADRs), serious adverse reactions (SARs) and serious adverse events (SAEs).

The start of the safety reporting window for the trial is the first prescription of statin treatment and the end point is the end of each participant’s participation in the trial. The safety follow-up will continue until the event is resolved.

The reporting of the ADRs can be based on participant reported symptoms (muscle symptoms or oedema) or based on changes to laboratory parameters (creatine kinase, serum-alanine aminotransferase, glycohaemoglobin).

Family physicians follow a predefined algorithm for managing adverse reactions, based on participant-reported symptoms and laboratory findings. Trial medication may be temporarily discontinued, with the subsequent decision to resume rosuvastatin 20 mg or switch to atorvastatin 40 mg once daily depending on whether the adverse reaction resolves.

Family physicians must report the ADR, SAR, SAE on REDCap. The sponsor will then assess the SARs and SAEs and if some are considered Suspected Unexpected Serious Adverse Reactions (SUSARs), report the SUSARs to Eudravigilance following set deadlines.

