### Outcomes

An overview of study objectives and outcome measures has been provided in Table 1.

**Table 1 T1:** Primary and secondary objectives and outcome measures

Objectives	Outcome measures
Primary objective:	Primary outcomes:
To assess the effectiveness of preventive statin treatment based on high CAD PRS on reducing the incidence of cardiovascular events and death.	Time to the first occurrence of Major Adverse Cardiovascular Events, using International Classification of Diseases (ICD-10) codes: ischaemic heart disease (I20–I25), stroke or transient ischaemia (I60–64, I69, G45), peripheral vascular occlusion and stenosis (I65–66, I67.2, I70, I73.9), revascularisation (Z95.1, Z95.5, Z95.8, Z95.9) or cardiovascular death (I00-I78).
Secondary objectives:	Secondary outcomes:
To assess all-cause mortality during the trial period.	Incidence rate of death from any cause among the study participants.
To assess the effect of the trial interventions on lowering cardiovascular risk factors.	Difference in CVD risk factors (LDL-cholesterol, blood pressure, BMI, waist circumference, smoking, alcohol consumption prevalence) by the end of the trial comparing the intervention and control arm.
To assess the adherence and acceptability to preventive statin treatment among high CAD PRS individuals.	Treatment adherence in the intervention arm based on prescriptions and purchases of statins (C10AA, C10BA) and self-reporting using the Medication Adherence Report Scale (MARS-5).^38^ Fidelity of implementation assessed by participant feedback, and adherence to programme activities (record analysis). Acceptability of the primary prevention programme across study participants. Satisfaction with study processes and results.
To assess the plasma concentration and side effects of rosuvastatin therapy depending on the presence of various genetic variants (in SLCO1B1, ABCG2, CYP2C9, CYP2C19, uridine diphosphate glycosyltransferase (UGT) family, SLCO1B3, SLCO2B1, ABCC2, ABCB11 genes).	Difference in plasma concentrations of rosuvastatin comparing study participants with specific genetic variants in the SLCO1B1, ABCG2, CYP2C9, CYP2C19, UGTs, SLCO1B3, SLCO2B1, ABCC2, ABCB11 genes Difference in rosuvastatin side effects between study participants with specific genetic variants in the SLCO1B1, ABCG2, CYP2C9, CYP2C19, UGTs, SLCO1B3, SLCO2B1, ABCC2, ABCB11 genes. Number of participants with adverse events and serious adverse events from statin therapy.

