### Data monitoring committee

The DMC is an independent multidisciplinary team comprising a biostatistician, a cardiologist and a primary care specialist. The DMC monitors participant safety and data integrity throughout the trial. The operational details of DMC activities will be described in the DMC Charter prior to the start of DMC work.

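### The safety wording contradicts itself and Table 1, and reported adverse reactions and serious adverse events have no defined control-arm window or reporter, so they cannot be compared by randomised arm

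*Protocol article*

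**What the plan says.** Four parts of the protocol article bear on this.

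- **Criteria for discontinuing or modifying allocated intervention.** Because the products are licensed and used within their licence, "the EE-PRS trial does not include any formal safety endpoints nor the documentation of adverse events". The next sentence, introduced as a consequence, commits the investigators to collecting and reporting adverse drug reactions (ADRs), serious adverse reactions (SARs) and serious adverse events (SAEs). On timing: "The start of the safety reporting window for the trial is the first prescription of statin treatment". On the reporter: "Family physicians must report the ADR, SAR, SAE on REDCap". The sponsor then assesses the SARs and SAEs.
- **Outcomes, Table 1.** Under the pharmacogenetic objective, one secondary outcome is "Number of participants with adverse events and serious adverse events from statin therapy". Separate rows list all-cause death among participants and, under the cost–utility objective, hospitalisations and length of stay.
- **Intervention arm and Control arm.** Side-effect assessments and blood tests at months 3, 12 and 60 are described for the intervention arm. For control participants: "Family physicians of the control arm participants will not be informed of their patients’ participation in the trial until the last visit at month 60".
- **Data monitoring committee.** "The DMC monitors participant safety and data integrity throughout the trial". Statistical methods adds that the committee periodically reviews accumulating efficacy and safety data.

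**The concern.** There are two problems, one of wording and one of design.

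The wording problem is that a reader cannot tell whether the trial has a safety outcome. One section says it has none and records no adverse events. The same section then collects SAEs, which are adverse events, and Table 1 makes a count of such events a secondary outcome.

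The design problem is that the described reporting stream exists, in effect, in one arm only. The trial offers a statin to people up to age 80 without diagnosed cardiovascular disease. Over 5 years in that age range many serious events will have nothing to do with treatment, and a count from treated participants alone cannot separate background events from drug effects. The reports also come from open-label physicians. For muscle, liver and diabetes harms, the areas the article itself monitors through symptoms and laboratory values, the trial could report a randomised estimate of benefit with no randomised estimate of harm beside it.

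**Working it through.** The article gives no safety rate, sample size or power to reproduce, so the main check sets the text side by side.

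**Step 1: is there a contradiction?**

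| Source | Safety endpoint? | Adverse events recorded? |
|---|---|---|
| Criteria for discontinuing, denial sentence | None (formal) | No |
| Same section, next sentence | Not stated | Yes: ADRs, SARs, SAEs |
| Table 1, pharmacogenetic row | Yes: secondary outcome | Yes: adverse and serious adverse events from statin therapy |

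The section conflicts with itself over SAEs and with Table 1 over whether a safety outcome exists. If events from statin therapy are read as adverse reactions, the conflict over documentation becomes largely one of terms. The conflict over having no safety endpoint remains.

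**Step 2: can reported events be compared by arm?** That needs a start date, a reporter and a prompt in each arm.

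| Element | Intervention arm | Control arm |
|---|---|---|
| Start of window | First statin prescription | None defined for a participant never prescribed a statin |
| Reporter | Family physician, on REDCap | Family physician, unaware of participation until month 60 |
| Side-effect assessment | Months 3, 12, 60 | None described before month 60 |

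A control participant who obtains a statin outside the trial might literally acquire a start date, but the prescriber would still not know that there was anything to report. So there is no usable control-arm stream for ADRs, SARs or SAEs.

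**Step 3: what can still be compared?** All-cause death and hospitalisations do not depend on a statin prescription, so both can be compared from randomisation. No row in Table 1 compares muscle, liver or diabetes diagnoses between arms.

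**Step 4: what precision would registry-coded outcomes give?** Inputs: 1350 per arm (Trial design); incidences of 5% and 40%, which are assumptions because the article gives none. The 95% half-width of a risk difference with equal incidence p in two arms of n is 1.96 × √(2p(1−p)/n).

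- p = 0.05: 1.96 × √(2 × 0.05 × 0.95 / 1350) = 0.016, or ±1.6 points.
- p = 0.40: 1.96 × √(2 × 0.40 × 0.60 / 1350) = 0.037, or ±3.7 points.

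These ignore the 10% dropout allowance in Sample size and power calculation. With 1350 × 0.9 = 1215 per arm, each half-width grows by √(1350/1215) = 1.054, to about ±1.7 and ±3.9 points.

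In terms of power (80%, two-sided 5%, 1350 per arm, assumed control risks), the detectable contrasts would be 1% against 2.4%, 5% against 7.6%, 10% against 13.5%, and 20% against 24.5%.

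**The case against.** The strongest reply is that the trial uses licensed products within their licence, that keeping control-arm physicians unaware is deliberate and protects the usual-care comparison, and that the denial sentence is only a clumsy way of saying that non-serious, unrelated events are not recorded. On that reading the Table 1 row is a count of adverse reactions in treated participants. It can be produced, and no between-arm comparison was promised. Most of this stands. The missing comparison is a design limitation and not a broken promise, and the reporting arrangement follows from a reasonable choice. The reply does not remove the conflict between having no safety endpoint and listing one.

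Four stronger readings are tempting, and the article does not support them.

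- **That no harm can be compared between arms.** All-cause death and hospitalisations can be.
- **That the Table 1 outcome cannot be produced.** It can, as a count among treated participants.
- **That unblinded physicians alone decide causality.** The sponsor also assesses SARs and SAEs.
- **That the data monitoring committee has no control rate.** Its operating details are left to a charter that is not shown, and registry-based primary events cover both arms.

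The supplementary data-collection table and the full protocol are also not shown. Control participants have baseline blood samples and final measurements at month 60, but the article does not say whether these include creatine kinase, alanine aminotransferase or glycohaemoglobin. A further control-arm source may therefore exist. If it does, the article's safety wording would still need correcting.

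The remedy is open to a fair objection too. Participants who are examined and have blood taken on schedule will collect more coded diagnoses, so a registry comparison of those codes could mislead unless this is stated.

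**Conclusion.** The concern holds in a limited form. The denial of safety endpoints and adverse-event documentation is inconsistent with the collection of ADRs, SARs and SAEs in the same section and with the Table 1 outcome. As described, those reported events have no defined control-arm window and no control-arm reporter before month 60, so they cannot be compared by randomised arm. No between-arm comparison of muscle, liver or diabetes harms is described.

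The primary analysis is not affected. What is forgone is a randomised estimate for those three areas, at roughly the precision shown above. Those figures are illustrations under assumed incidences and do not measure the defect. The contradiction rests on the text alone. The statement about control-arm data rests on the article as it stands, without the supplement, the full protocol or the committee charter. The change is cheap and should be made.

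**What to change.** 1. **Reconcile the text.** Relabel the Table 1 item as ADRs, SARs and SAEs among participants prescribed the trial statin, descriptive only. Reword the denial so that it states what is and is not recorded.
2. **Add a between-arm safety comparison.** Count registry-coded muscle, liver and diabetes diagnoses, and report the hospitalisations already listed under resource use as a safety outcome. Count all of these from randomisation to month 60 in both arms, by intention to treat, and supply them by arm to the data monitoring committee.
3. **State the limits beside the results.** Registry codes miss mild symptoms. The intervention arm's scheduled blood tests and side-effect visits can raise coded liver, muscle and diabetes diagnoses there. All-cause hospitalisation and death are less prone to this and should be read as the firmer comparisons.

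The cost is a few further ICD-10 queries in the registry analysis already planned for both arms, some protocol and analysis-plan wording, and one more table. No visits are added, and control-arm physicians stay unaware.

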### Adherence to intervention

As this is a pragmatic trial, we will not be counting issued packages of the study medication or pills taken by study participants in the intervention arm but rather study nurses will be monitoring compliance using a specially designed database on the numbers of issued prescriptions and procured medicines by study participants. The study nurses’ telemedicine appointments will help to ensure better adherence and motivation to take the IMPs by study participants. In addition, qualitative measures of treatment adherence will be used such as the 5-item Medication Adherence Report Scale (MARS-5) in participant online surveys. Statin procurement is also tracked in the real-life control arm via the national prescription database, enabling quantification of contamination during the study period.

### Outcomes

An overview of study objectives and outcome measures has been provided in Table 1.

**Table 1 T1:** Primary and secondary objectives and outcome measures

Objectives	Outcome measures
Primary objective:	Primary outcomes:
To assess the effectiveness of preventive statin treatment based on high CAD PRS on reducing the incidence of cardiovascular events and death.	Time to the first occurrence of Major Adverse Cardiovascular Events, using International Classification of Diseases (ICD-10) codes: ischaemic heart disease (I20–I25), stroke or transient ischaemia (I60–64, I69, G45), peripheral vascular occlusion and stenosis (I65–66, I67.2, I70, I73.9), revascularisation (Z95.1, Z95.5, Z95.8, Z95.9) or cardiovascular death (I00-I78).
Secondary objectives:	Secondary outcomes:
To assess all-cause mortality during the trial period.	Incidence rate of death from any cause among the study participants.
To assess the effect of the trial interventions on lowering cardiovascular risk factors.	Difference in CVD risk factors (LDL-cholesterol, blood pressure, BMI, waist circumference, smoking, alcohol consumption prevalence) by the end of the trial comparing the intervention and control arm.
To assess the adherence and acceptability to preventive statin treatment among high CAD PRS individuals.	Treatment adherence in the intervention arm based on prescriptions and purchases of statins (C10AA, C10BA) and self-reporting using the Medication Adherence Report Scale (MARS-5).^38^ Fidelity of implementation assessed by participant feedback, and adherence to programme activities (record analysis). Acceptability of the primary prevention programme across study participants. Satisfaction with study processes and results.
To assess the plasma concentration and side effects of rosuvastatin therapy depending on the presence of various genetic variants (in SLCO1B1, ABCG2, CYP2C9, CYP2C19, uridine diphosphate glycosyltransferase (UGT) family, SLCO1B3, SLCO2B1, ABCC2, ABCB11 genes).	Difference in plasma concentrations of rosuvastatin comparing study participants with specific genetic variants in the SLCO1B1, ABCG2, CYP2C9, CYP2C19, UGTs, SLCO1B3, SLCO2B1, ABCC2, ABCB11 genes Difference in rosuvastatin side effects between study participants with specific genetic variants in the SLCO1B1, ABCG2, CYP2C9, CYP2C19, UGTs, SLCO1B3, SLCO2B1, ABCC2, ABCB11 genes. Number of participants with adverse events and serious adverse events from statin therapy.
To assess the resource use, cost and cost–utility of preventive statin treatment based on CAD PRS compared with the standard of practice in primary care.	Utilisation of healthcare resources (non-trial physician and cardiologist visits, hospitalisations, length of stay, healthcare and informal resource use, direct healthcare costs). Productivity costs from the iMTA Productivity Cost Questionnaire (iPCQ) .^39^ Number of participants who withdrew or dropped out from the study. Utilities from the EuroQol 5-dimension 5-level questionnaires (EQ-5L-5D) for calculating quality-adjusted life-years. Incremental cost-effectiveness ratio.
To assess the bidirectional relationship between statin therapy and the gut microbiome, specifically focusing on two intertwined aspects: (1) the mechanisms by which statins modulate gut microbiome composition and function and (2) the influence of the gut microbiome on the therapeutic efficacy of statins.	Association between gut microbiome composition and functionality and statin side effect occurrence. Change from baseline in gut microbiome composition and functionality in statin vs control arm. Association between baseline gut microbiome composition and functionality and statin treatment efficacy.

BMI, body mass index; CAD, coronary artery disease; CVD, cardiovascular disease; LDL, low-density lipoprotein; MACE, major adverse cardiovascular event; PRS, polygenic risk score; SAE, serious adverse event.

### Participant timeline

The trial runs from March 2025 to March 2031, with each participant followed for 5 years from their enrolment date. A follow-up registry-based analysis will be conducted 3 years after the end of the trial (Figure 1).

**Figure 1 F1:**
[figure not shown]
Participant timeline.

### Sample size and power calculation

The power calculations are based on the EstBB cohort, accounting for the observed age and risk factor distribution and the estimated effect sizes. The sampling frame is based on all EstBB gene donors (211 739 individuals).^24 25^ The CAD PRS have been previously calculated for all participants based on the method described by Patel *et al*.^26^

The study target sample includes men aged 45–80 years and women aged 55–80 years who are within the top 20% CAD PRS. The sample used for modelling (n=36 405, 17 861 men, 18 544 women) satisfied the following criteria:

No prevalent CVD (as defined in the protocol), no missing values in body mass index, systolic blood pressure, smoking level and PRS;Age 45–80 at agreement for men and 55–80 for women.

The actual EstBB cohort was used for sample size calculation, assuming that the study sample will be a random sample from all eligible participants. The potential outcome distributions were obtained based on statistical simulation, assuming that the age-specific 5-year major adverse cardiovascular event (MACE) incidence without statin treatment will be similar to what has been observed in the cohort (the Weibull distribution appeared to provide an appropriate approximation) and that the statin treatment will reduce the outcome hazard up to 30%.

Based on an anticipated hazard reduction of 30% with statin treatment and allowing for up to 10% dropout, a recruitment target of 2700 participants is set to ensure a minimum of 80% statistical power.

### Recruitment

The identification of study participants begins with a prescreening of EstBB cohort participants based on set eligibility criteria. As a next step, the primary care physicians with the highest number of potentially eligible patients are contacted to assess their interest in facilitating the trial activities. Primary care centres that agree to participate are contracted for the trial, after which outreach to potentially eligible individuals will begin.

The EstBB will send out invitation emails and SMS messages to potentially eligible individuals, including a link to the MyGenome portal, where they can read recruitment materials describing the trial and its interventions or watch short videos where research team members present the study in an easy-to-understand language and format.^27^

On reading about the study, the individuals must indicate by ticking a box in the MyGenome portal whether they would like to be contacted by a study nurse. All individuals who show interest in participation are contacted via phone call by a study nurse who screens for eligibility and if the individual passes, books them an appointment for a final eligibility assessment and consenting meeting with a study physician. These meetings take place either as a video conference call or in person during which the physician taking the consent will ask eligibility questions from the potential participant and note them down in the study portal. Only individuals who pass this final face-to-face eligibility screening with the physician are then eligible to provide informed consent (either by signing the informed consent form (ICF) on paper or digitally in the MyGenome portal).

The ICF includes two optional questions: one asking participants whether they wish to provide stool samples at months 0 and 3 for microbiome analysis, with samples stored indefinitely at the EstBB for future research; and one asking whether they consent to their registry data being used in a 3-year post-trial follow-up analysis. Only data from participants who explicitly opt in will be included in the follow-up analysis.

Once an eligible participant has signed the ICF, they will be automatically randomised to the intervention or control arm and their eligibility data will be sent from the EstBB database to the trial database REDCap.

### Randomisation

The randomisation unit is an individual participant. The statistician will use a computer-generated randomisation algorithm (permuted block technique) to generate the randomisation sequence. The allocation sequence will be generated by a statistician independent of participant eligibility assessment and enrolment.

The EstBB then uses the randomisation sequence to automate participant allocation to study arms. On signing the ICF, each eligible participant is automatically assigned to either the intervention or control arm and their eligibility data transferred from the EstBB to the trial database REDCap.

